#### Legal reporting requirements of the sponsor

It is the duty of the Safety Desk to ensure that Ethics Committee, competent authority and participating investigators are informed of all suspected unexpected serious adverse reactions (SUSARs) and all other relevant safety information in accordance with legal requirements.

It is the duty of the Safety Desk to inform the marketing authorization holder involved according to stipulation.

The Coordinating Investigator is responsible for the ongoing safety evaluation of the trial. The Safety Desk will inform the Coordinating Investigator immediately about any relevant safety information coming to its knowledge as will the Coordinating Investigator inform the Safety Desk. In case of other safety relevant issues (besides SUSARs) which require expedited reporting, the Safety Desk will support the Coordinating Investigator in submitting an appropriate report in due time.

The Coordinating Investigator is responsible for providing the updated benefit-risk assessment of the trial for the Annual Safety Report (Development Safety Update Report, corresponding parts to Part 1 of the previous Annual Safety Report). The Safety Desk is responsible for preparing all other parts of the report, finalizing it and submitting it to the competent authority and ethics committee in due time.

The Safety Desk will provide information for the Safety Committee as requested (see also 9.1).

## 7.3 Warnings and Precautions

### 7.3.1 Investigational product (BIBF 1120)

#### 7.3.1.1 Summary of known adverse drug reactions

Adverse reactions have been collected from phase I/II monotherapy studies with BIBF 1120 and combination studies of BIBF with cytotoxic agents. A summary of all adverse reactions is listed below [16].

#### Gastrointestinal adverse events

Frequent gastrointestinal adverse events included nausea (55%), diarrhea (43.9%), vomiting (39.8%), fatigue (24.8%), asthenia (15.0%) and abdominal pain (11.8%). Grade 3/4 adverse reactions of the above listed occurred in 0.7 to 3.3% in monotherapy studies and between 2.1 and 9.5% in the combination studies with Docetaxel / Prednisone, Carboplatin / Paclitaxel or Pemetrexed. All gastrointestinal adverse events were fully reversible.

#### Elevation of transaminases

While 10 – 15% of patients treated with doses 250mg of BIBF 1120 bidaily experienced a grade 3/4 transaminase elevation, no grade 3/4 transaminase elevation was observed at doses of 200 mg bidaily or lower. Transaminase elevations grade  $\leq 2$  were rarely seen at doses of 200 or 150 mg BIBF bidaily, either as monotherapy or in combination with chemotherapy. All transaminase elevations normalized after dose reduction or interruption of BIBF 1120.

#### Infections

Infectious complications were a frequent event both in the monotherapy and in the combination therapy. However, only few infections (app. 4%) were considered drug related.

#### Thrombembolic and cardiac events

The frequency of drug related thromboembolic events was low across all completed studies using BIBF 1120 monotherapy, and the frequency of thromboembolic adverse events regardless of relatedness did not seem to exceed the expected rate in the patients with advanced solid tumors.

#### Hypertension

Blood pressure elevation occurred in app. 10% of all patients, the vast majority with grade 1-2. Very rarely a grade 3/4 hypertension was seen, which suggests a relatively low hypertensive potential of BIBF 1120 as compared to other antiangiogenic compounds.

## Dermatological events

Based on the current clinical data, the risk for light induced dermatological reactions is considered to be low.

## Bleeding events

Events recorded bleeding events encoded the following: anemia, epistaxis, haemoptysis, hemorrhage, prolonged bleeding time and hematoma considered to be treatment-related occurred in 6% in the monotherapy and 13% in the combination therapy studies.

Further details of the side effect profile of BIBF 1120 can be found in the current version of the Investigator's Brochure (IB). The IB is updated on a regular basis.

### **7.3.2 Cytarabine**

For information of all known adverse drug reactions please refer to the 'Fachinformation Deutschland' in its latest version.

## 8 STUDY OUTCOME AND STATISTICAL ANALYSIS

### 8.1 Power and Sample Size Calculation

In phase II of the study the primary endpoint is the overall response rate (ORR) in the whole study population. In the primary analysis the following null hypothesis will be tested against a one-sided alternative on the significance level  $\alpha=0.025$ .

$H_0$ : ORR $\leq$ 25% versus  $H_1$ : ORR $>$ 25%

The ORR under BIBF 1120 treatment is expected to depend on the absence or presence of a Flt3-mutation. In Flt3-mutated and Flt3-wildtype patients the expected ORR is ORRFlt3-mutated=50% and ORRFlt3-wildtype=35%, respectively. In present data of a comparable population 13% of study patients showed a Flt3-mutation. Thus across all study patients the expected ORR amounts to  $ORR = 50\% \cdot 0.13 + 35\% \cdot 0.87 = 37\%$ . A single stage design with fixed sample size was chosen. Given the above expected ORR=37%, in order to provide a  $1-\beta=80\%$  power of the primary hypothesis test, 111 evaluable patients are required to be included in the study, i.e. expectedly 14 Flt3-mutated and 97 Flt3-wildtype patients. 11 patients (10%) are anticipated not to be evaluable in the primary analysis due to missing data. Thus a total of 122 patients will be recruited into the phase II part of study.

Power calculations were performed using SAS version 9.2 (SAS Institute Inc., Cary, NC, USA).

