### 8.2 Statistical Analysis Plan

The Statistical Analysis Plan (SAP) will be established without having insight into study data. In the SAP the statistical analyses are described in detail. The primary analysis will be performed using the one-sample (exact) Binomial test, applied according to the intention to treat principle (ITT). This means that every patient included into the study will be evaluated, even if he or she did not receive study medication, or any other violations of the study protocol occurred. Results of primary ITT analyses provide confirmatory statistical evidence. In addition to the ITT analysis a per protocol analysis (PP) will be performed. In the PP analysis only those patients are included who could be treated with full adherence to the protocol. Beyond the primary analysis, pre-specified analyses of secondary endpoints will be performed with appropriate  $\alpha$ -adjustment due to multiplicity. Further exploratory analyses will be performed and interpreted according to the relatively low level of scientific evidence provided.

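### With the exact binomial test named in section 8.2, 111 evaluable patients give about 75–76% power, not the 80% stated in section 8.1

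*Protocol*

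**What the plan says.** Protocol section 8.1 sets the phase II primary hypothesis as ORR of at most 25% against ORR above 25%: "the following null hypothesis will be tested against a one-sided alternative on the significance level" 0.025. The expected rate is a mixture of 50% in Flt3-mutated and 35% in wildtype patients. It is weighted by earlier data in which "13% of study patients showed a Flt3-mutation", and the protocol gives the result as 37%. "A single stage design with fixed sample size was chosen".

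For 80% "power of the primary hypothesis test", section 8.1 states that "111 evaluable patients are required to be included in the study". It then adds an allowance: "11 patients (10%) are anticipated not to be evaluable in the primary analysis due to missing data". That brings recruitment to 122. SAS 9.2 is named as the software, without a procedure or formula.

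Section 8.2 fixes the test: "The primary analysis will be performed using the one-sample (exact) Binomial test". It is applied by intention to treat (ITT) to all patients included, whether or not they were treated or followed the protocol.

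**The concern.** Section 8.1 presents the 80% as a property of the primary test, and section 8.2 says which test that is. The exact binomial test works with whole-number cut-offs. Its real type I error therefore usually lies below the nominal level, and its power lies below what a smooth approximation suggests. If 111 was obtained without allowing for this, the stated power is not the power of the planned analysis.

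This is the only confirmatory test in a single-arm trial. At stake is the stated chance of missing a true response rate of 37%: 20% according to the protocol, but about 24 to 25% for the exact test at 111 patients, before any question of how missing data are counted.

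**Working it through.** **Inputs, all from Protocol sections 8.1 and 8.2.** Null rate p0 = 0.25; one-sided alpha 0.025; target power 80%; n = 111 evaluable; 11 expected non-evaluable; 122 recruited; exact binomial test. Expected rate p1 = 0.50 × 0.13 + 0.35 × 0.87 = 0.065 + 0.3045 = 0.3695, printed as 37%. Both values are carried below.

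**Step 1: reproduce the protocol's 111.** The one-sample normal approximation without continuity correction is

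n = [(1.960 × √(p0(1 − p0)) + 0.8416 × √(p1(1 − p1))) / (p1 − p0)]²

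- p1 = 0.3695: [(1.960 × 0.4330 + 0.8416 × 0.4827) / 0.1195]² = 110.28, rounded up to **111**. Approximate power at 111 is 80.2%.
- p1 = 0.37: [(1.960 × 0.4330 + 0.8416 × 0.4828) / 0.12]² = 109.38, rounded up to 110. Approximate power at 111 is 80.5%.

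Other common formulas do not give 111: alternative variance only 128 to 129, null variance only 103 to 104, arcsine 116 to 117, continuity-corrected 118 to 119. The uncorrected formula at the unrounded rate matches exactly.

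**Step 2: the exact test at 111.** The rule is to reject at the smallest count r with P(X ≥ r | n, 0.25) ≤ 0.025.

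| Cut-off at n = 111 | P(X ≥ r) at 25% | P(X ≥ r) at 37% |
|---|---|---|
| ≥ 37 | 0.0303 (exceeds 0.025) | 81.5% |
| ≥ 38 | 0.0186 | 75.7% |

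The cut-off is therefore 38. Power is 75.7% at 37% and 75.4% at 36.95%, a type II error of 24.3% to 24.6%. The cut-off that would pass 80% breaks the alpha limit.

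**Step 3: neighbouring sizes.**

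| Patients analysed | Reject at | True alpha | Power at 37% | Power at 36.95% |
|---|---|---|---|---|
| 111 | ≥ 38 | 0.0186 | 75.7% | 75.4% |
| 113 | ≥ 38 | 0.0248 | 79.9% | 79.6% |
| 114 | ≥ 39 | 0.0175 | 76.1% | 75.8% |
| 116 | ≥ 39 | 0.0233 | 80.2% | 79.9% |
| 119 | ≥ 40 | 0.0219 | 80.5% | 80.1% |
| 122 | ≥ 41 | 0.0206 | 80.7% | 80.4% |
| 124 | ≥ 42 | 0.0169 | 79.2% | 78.8% |
| 128 | ≥ 43 | 0.0182 | 81.3% | 81.0% |

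The smallest size with at least 80% is 116 (at 37%) or 119 (at 36.95%). Power stays at or above 80% for every size only from 128 upward.

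**Step 4: the 122 recruited, with 11 non-evaluable.** The protocol does not say how these 11 enter the ITT analysis, so three cases are shown at a 37% response rate:

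- All 122 analysed and all with a 37% chance of response: reject at ≥ 41, alpha 0.0206, power 80.7%.
- The 11 excluded, leaving 111: reject at ≥ 38, power 75.7%.
- The 11 kept in the denominator as non-responders (an assumption): at least 41 responders are needed from the 111 evaluable, P(X ≥ 41 | 111, 0.37) = 54.1%.

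**The case against.** The strongest defence is that 122 patients are recruited, ITT analyses all of them, and 122 gives 80.7%. The arithmetic is right, but the condition is not one the protocol states. Section 8.1 attaches the 80% to 111 patients and expects 11 of the 122 to be non-evaluable in the primary analysis. The 80.7% needs all 122 to count with a 37% chance of response. Neither way of handling the 11 shown above reaches 80%.

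A second defence is that the gap is partly discreteness: 113 patients would give 79.9%. That is true, and it limits the practical weight of the point. The steps nevertheless belong to the test the protocol chose, and at the stated 111 the figure is 75–76%.

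Third, the test remains valid. Its true type I error of 0.0186 is below 0.025, so a reader who inferred that a positive result would be unreliable would be wrong. The fault lies in the stated power.

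Two other readings go further than the document allows. One is that the size was in fact derived from a normal approximation. The match at 36.95% is exact, but the same formula gives 110 at the printed 37%, and the protocol names only the software. The other is that the trial's power simply is 54%. That follows only if the 11 count as non-responders, a rule the protocol does not set and the statistical analysis plan may settle either way. Leaving that rule to the analysis plan is not itself a fault.

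**Conclusion.** The power statement in section 8.1 is wrong as written. For the exact binomial test in section 8.2, with 111 patients, one-sided alpha 0.025 and rates of 25% and 37%, power is 75.7% (75.4% at 36.95%), 4 to 5 points below 80%. This needs no input from outside the protocol and does not depend on how 111 was obtained.

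The step to 122 does not repair the statement under the protocol's own expectation of 11 non-evaluable patients. Power is then about 76% or about 54%, depending on whether they are excluded or counted as non-responders. The 80.7% at 122 holds only with complete data and a 37% response rate throughout. The hypothesis, the choice of test and control of the type I error are unaffected.

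**What to change.** Restate the power in section 8.1 for the exact test: with 111 analysed, reject at 38 or more responders, true alpha 0.0186, power about 75–76%. If 122 is also quoted (reject at 41 or more, true alpha 0.0206, power 80–81%), say that this holds only if all 122 are analysed and the 37% rate applies to all of them. Give the power under the rule that will be used for the expected 11 non-evaluable patients, and do not claim that 122 secures 80%. Name the method behind the sample size.

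The cost is a change of wording and a less favourable power figure. Whether to accept that power or enlarge the trial is then an open decision for the sponsor. If 80% is to be kept for evaluable patients, the exact test needs at least 116 (at 37%) or 119 (at 36.95%) analysed, before any allowance for missing data. These sizes must be hit exactly, because power dips below 80% again at some larger sizes up to 127.

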#### Indeterminate cause:

- Patients who die  $< 7$  days post CT; Patients who die  $> 7$  days post CT with no PB blasts, but bone marrow examination not performed or not evaluable; Patients who do not complete the first course of therapy

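### Section 8.1 removes 11 of 122 patients from a primary analysis that section 8.2 runs on everyone, so the stated 80% power depends on which patients the 37% response rate describes

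*Protocol*

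**What the plan says.** Protocol section 8.1 sets a one-sided exact level of 0.025 for a null ORR of 25% in phase II. It builds an expected ORR of 37% from 50% in Flt3-mutated and 35% in wild-type patients, with a 13% mutated share. From this it concludes that "111 evaluable patients are required to be included in the study" for 80% power. It then states that "11 patients (10%) are anticipated not to be evaluable in the primary analysis due to missing data" and arrives at 122 recruited.

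Section 8.2 names the one-sample exact binomial test as the primary analysis, applies it by intention to treat, and gives confirmatory status to that analysis alone. It spells out the set: "This means that every patient included into the study will be evaluated, even if he or she did not receive study medication", and other protocol violations do not remove a patient either.

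Two further places bear on patients without an assessment. Section 8.5 defines ORR as the share of patients who achieve CR, CRp or CRi at any time during participation. Section 8.4.1 places an indeterminate-cause category in the treatment-failure part of the response criteria. It covers early deaths, later deaths without an evaluable marrow, and "Patients who do not complete the first course of therapy".

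**The concern.** A patient cannot be both outside the primary analysis for missing data and evaluated in it. The choice of denominator affects the power and can decide the result. This is an uncontrolled trial with a single pass/fail threshold. For example, 38 responders among 111 evaluable patients (34.2%) would reject the null hypothesis, while the same 38 among 122 (31.1%) would not.

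If the text stays as it is, section 8.1 offers support for an evaluable-only denominator and section 8.2 for the full one. The stated 80% is also not tied to the analysis that will carry the confirmatory claim.

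**Working it through.** **Inputs.** From section 8.1: null ORR p0 = 0.25, one-sided level 0.025, target power 80%, 111 evaluable, 11 not evaluable, 122 in total. The expected ORR is 0.13 × 50% + 0.87 × 35% = 36.95%, rounded in the protocol to 37%. From section 8.2: exact binomial test, ITT.

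**1. The plan's own figure.** The normal approximation is n = [z(0.975)·√(p0(1−p0)) + z(0.80)·√(p1(1−p1))]² / (p1−p0)².

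- With p1 = 0.3695: n = [1.960 × √0.1875 + 0.8416 × √(0.3695 × 0.6305)]² / 0.1195² = (0.8487 + 0.4062)² / 0.1195² = 110.3, so 111.
- With p1 = 0.37: 109.4, so 110.
- Allowance: 111 × 1.10 = 122.1, so 122. The 11 are 10% of 111 and 9.0% of 122.

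The 111 reproduces, but as a normal-approximation figure rather than one for the exact test.

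**2. Exact test on 111 evaluable patients.** The smallest k with P(X ≥ k | 111, 0.25) ≤ 0.025 is 38 (actual level 0.0186). Power P(X ≥ 38 | 111, 0.37) = 75.7%, or 75.4% at 36.95%.

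**3. Exact ITT test on 122.** The smallest k with P(X ≥ k | 122, 0.25) ≤ 0.025 is 41, i.e. 33.6% observed (actual level 0.0206). The power depends on the population to which 37% applies.

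*37% in all 122 included patients:* P(X ≥ 41 | 122, 0.37) = 80.7%.

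*37% only in evaluable patients, with m others counted as failures:* the ITT response rate is 0.37 × (122 − m)/122.

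| m counted as failures | ITT ORR | Power |
|---|---|---|
| 0 | 37.0% | 80.7% |
| 2 | 36.4% | 76.7% |
| 5 | 35.5% | 69.9% |
| 11 | 33.7% | 53.9% |

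Treating the 11 as fixed failures, P(X ≥ 41 | 111, 0.37), gives 54.1%, in practice the same.

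**4. What would be needed for 80% in the last row.** An ITT ORR of about 36.9% gives 80% power on 122. With 11 failures that means 36.9% × 122/111 = 40.6% among evaluable patients. Alternatively, at 37% among evaluable patients and 9.0% missing counted as failures, the total would have to be about 215 (first size to reach 80%) to 231 (power stays at or above 80% from there on).

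**The case against.** A reader might infer that the trial simply has 54% power. The protocol does not support that as an unconditional statement, for four reasons.

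- Section 8.1 presents the 37% as the rate expected over all patients of the study and sets the endpoint in the whole study population. Taken at its word, the ITT test on 122 has 80.7% power and nothing is lost.
- The 11 are described only as missing data. If early deaths and incomplete first courses are already failures by definition, a whole-population rate of 37% may include them, and multiplying by 111/122 could subtract them twice.
- All 11 failing is the extreme case. Response counts at any time, treatment runs for up to six cycles with a marrow in each, and section 5.4.1 allows a failed aspirate to be repeated, so one missed assessment does not make a patient unassessable.
- No sentence says that missing means non-response. That follows from the ITT wording, the ORR definition and the failure list. A statistical analysis plan, which is not shown, could state the rule.

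These points stand, and they make the 54% conditional. They do not remove the conflict. If 37% covers everyone, ITT loses nobody and the 10% allowance serves no purpose. The allowance makes sense only if the 111 and the 37% describe evaluable patients, and that is the reading on which power falls. The protocol itself fixes both statements, so this is not detail left to a later plan.

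A reader might also infer that an evaluable-only analysis would mainly exclude early deaths and so inflate the ORR. The protocol gives no breakdown of the 11, so that cannot be said. Nor is the type I error of the confirmatory test in doubt: its actual level is 0.0206.

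**Conclusion.** The contradiction between sections 8.1 and 8.2 is real and touches the confirmatory analysis. The power of the ITT test on 122 patients lies between about 54% and about 81%. The upper end assumes that 37% is the response rate in every included patient. The lower end assumes that 37% applies only to the 111 evaluable patients and that the other 11 all count as failures; with fewer such failures power lies in between. Reading the analysis as evaluable-only does not rescue the stated figure either, because the exact test then has 75.7%. The 80% holds only on the first assumption, and there the allowance for non-evaluable patients has no role.

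**What to change.** Keep ITT on all 122 as the confirmatory analysis and state in section 8.2 that missing, unevaluable or never-treated patients count as non-responders. In section 8.1, delete the statement that 11 patients are not evaluable in the primary analysis. Put in its place the decision threshold (at least 41 responders of 122) and the power under both assumptions: about 81% if the ORR is 37% in all included patients, and about 54% if 37% applies only to evaluable patients and 11 are missing. Report the evaluable-only ORR as a sensitivity analysis.

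The cost is protocol and analysis-plan wording and a less favourable power statement, with no added patients. The rewording restores no power. If the sponsor believes the less favourable assumption, the consequence for the sample size is the one shown in step 4, and that should be a deliberate decision.

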### 8.2 Statistical Analysis Plan

The Statistical Analysis Plan (SAP) will be established without having insight into study data. In the SAP the statistical analyses are described in detail. The primary analysis will be performed using the one-sample (exact) Binomial test, applied according to the intention to treat principle (ITT). This means that every patient included into the study will be evaluated, even if he or she did not receive study medication, or any other violations of the study protocol occurred. Results of primary ITT analyses provide confirmatory statistical evidence. In addition to the ITT analysis a per protocol analysis (PP) will be performed. In the PP analysis only those patients are included who could be treated with full adherence to the protocol. Beyond the primary analysis, pre-specified analyses of secondary endpoints will be performed with appropriate  $\alpha$ -adjustment due to multiplicity. Further exploratory analyses will be performed and interpreted according to the relatively low level of scientific evidence provided.

### 8.3 Number of patients

Under the above assumptions (see 8.1), total accrual to the controlled phase of this trial is planned for 122 patients.

### 8.4 Efficacy

Evaluation of bone marrow aspirate, peripheral blood counts and differentials are used to assess the efficacy of the study medication.

#### 8.4.1 Response criteria

Response criteria are defined according to the Revised Recommendations of the International Working Group for Diagnosis, Standardization of Response Criteria, Treatment Outcomes, and Reporting Standards for Therapeutic Trials in Acute Myeloid Leukemia [18].

##### Responding Patients:

Morphologic complete remission (CR):

- Platelet count >100,000/ $\mu$ l
- Granulocyte count of >1,000/ $\mu$ l
- Bone marrow (aspirate with marrow spicules): < 5% blasts, Absence of Auer rods
- No evidence of persisting leukemia by flow cytometry (Sensitivity: 5%)
- Absence of extramedullary leukemia
- Transfusion independent stable hemoglobin value

Complete remission with incomplete platelet recovery (CRp):

- Granulocyte count of >1,000/ $\mu$ l
- Bone marrow (aspirate with marrow spicules): < 5% blasts, Absence of Auer rods
- No evidence of persisting leukemia by flow cytometry (Sensitivity: 5%)
- Absence of extramedullary leukemia
- Peripheral blood with no blast cells and less than 100,000/ $\mu$ l platelets

Complete remission with incomplete neutrophil recovery (CRi):

- Bone marrow (aspirate with marrow spicules): < 5% blasts, Absence of Auer rods
- No evidence of persisting leukemia by flow cytometry (Sensitivity: 5%)
- Absence of extramedullary leukemia
- Peripheral blood with no blast cells and less than 1,000/ $\mu$ l granulocytes irrespective of the platelet count
- Molecularly negative (no detection of pre-treatment genetic markers with a methodology providing a sensitivity of at least 1:10^3)

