### 3.2.2 Phase II

Primary endpoint:

- to evaluate the overall response rate (ORR, consisting of: CR, CRp and CRi as defined by IWG criteria) of the whole study population

Secondary endpoints:

- to compare the ORR rate of the Flt3-mutated patients versus the Flt3-wildtype patients and within different cytogenetic risk groups
- to evaluate the CR rate of the whole study population
- to compare the CR rate of the Flt3-mutated patients versus the Flt3-wildtype patients and within different cytogenetic risk groups
- to evaluate the one-year overall survival (OS) of the whole study population

---

 response criteria by the International Working Group (IWG) are defined as:

- Complete remission (CR): less than 5% bone marrow blasts and regeneration of both peripheral neutrophils to  $>1,000/\mu\text{l}$  and platelets to  $>100,000/\mu\text{l}$
- Complete remission with incomplete platelet recovery (CRp): less than 5% bone marrow blasts and regeneration of peripheral neutrophils to  $>1,000/\mu\text{l}$  with a platelet count of  $<100,000/\mu\text{l}$
- Complete remission with incomplete neutrophil recovery (CRi): less than 5% bone marrow blasts with a neutrophil count of  $<1,000/\mu\text{l}$  with or without platelet recovery

- to compare the one-year overall survival (OS) of the Flt3-mutated patients versus the Flt3-wildtype patients and within different cytogenetic risk groups
- to evaluate the relapse-free survival (RFS) of the responding patients
- to evaluate the time to response (CR, CRp or CRi) of the responding patients
- to evaluate the toxicity in the whole study population
- to evaluate the development of biomarkers indicating the course of disease, including genetic, epigenetic, transcriptional, protein and phosphoprotein markers in leukemic blasts, bone marrow, peripheral blood cells, serum and plasma, and bone marrow microvessel density.

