#### 6.1.2 Evaluations during treatment

*(for full details about timepoints of evaluations please refer to 6.2)*

- Control of CBC (with differential and platelets) weekly
- Bone marrow aspirate between day 24 and day 28 of each cycle
- Asservation of vital bone marrow cells (Ficoll-treated bone marrow), bone marrow RNA, DNA and protein lysates, serum and plasma in a central tissue repository.
- Control of coagulation and serum chemistries
- Performance status

- Physical examination
- Body weight
- Diagnostic procedures i.e. in case of severe infections will follow standard procedures
- Baseline evaluations will be repeated prior to each following course if necessary in the investigator's opinion
- ECG as often as necessary in the investigator's opinion

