#### 6.3.2 Requested material and shipment modalities

At diagnosis and during follow-up bone marrow evaluations, please collect for central diagnostics and central tissue and serum repository:

|                                                             |                                                                                                                     |
|-------------------------------------------------------------|---------------------------------------------------------------------------------------------------------------------|
| Central cytomorphological review (on request)        | 5 ml bone marrow aspirate in EDTA
at least 4 unstained bone marrow smears
2 unstained peripheral blood smears |
| Central immunophenotyping (on request)               | 6-8 ml heparinized bone marrow                                                                                      |
| Central molecular diagnosisa (on request) | 6-8 ml heparinized bone marrow                                                                                      |
| Central histologyb (mandatory)            | 1 bone marrow biopsy, fixed in 'Kölner Lösung'                                                                      |
| Central cell repository (mandatory)                  | 2 x 6-8 ml heparinized bone marrow
20 ml heparinized peripheral blood
9 ml serum                              |

a At diagnosis. During follow-up only in case of detection of a molecular marker at diagnosis

b At diagnosis and at the time of response confirmation one month after begin of observation period in responding patients

The fixation solution ‘Kölner Lösung’ will be sent to the participating centers at the time of study initiation, every 6 weeks, and additionally upon request ([contact], or [contact]).

Shipment is recommended from Monday through Thursday, if possible in the morning by express delivery or courier to the following addresses:

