#### Overall response rate (ORR):

Proportion of patients who achieve either a complete remission (CR), a CRp or a CRi, as defined above, at any time point during study participation.

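### The primary endpoint has two conflicting definitions of response (3.2.2 footnote versus 8.4.1), and nothing says how a response marrow without flow cytometry is classified

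*Protocol*

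**What the plan says.** **Two definitions.** The footnote to Protocol 3.2.2, attached to the primary endpoint, opens its definition of CR with "less than 5% bone marrow blasts and regeneration of both peripheral neutrophils to" more than 1,000/µl, together with platelets above 100,000/µl. CRp and CRi are built from the same elements: marrow blasts and counts. Section 8.4.1 lists under each of CR, CRp and CRi "No evidence of persisting leukemia by flow cytometry (Sensitivity: 5" percent). Its CRi list ends with a requirement of molecular negativity. Section 8.5 defines ORR as: "Proportion of patients who achieve either a complete remission (CR), a CRp or a CRi, as defined above, at any time point during study participation". Following 8.4.1 as it does, this makes the longer list the operative one.

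**What is measured at response.** Section 8.4 states: "Evaluation of bone marrow aspirate, peripheral blood counts and differentials are used to assess the efficacy of the study medication". Flow is not among these sources. Section 6.1.1 lists immunophenotyping before treatment. Section 6.1.2 asks for "Bone marrow aspirate between day 24 and day 28 of each cycle" and does not itemise flow; nor do 6.1.3, 6.1.4 or Table 2. Section 6.1.2 lets baseline evaluations be repeated before a later course at the investigator's discretion. Section 6.3.2 offers "Central immunophenotyping (on request"), with material from follow-up marrows. Section 6.3.4 asks for local typing in all patients without naming a time point.

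**Two smaller points in 8.4.1.** CRp carries the item "Peripheral blood with no blast cells and less than 100,000" platelets per µl, and CRi also excludes blood blasts, but the CR list has no such item. The neutrophil and platelet limits are strict inequalities on both sides (> and <).

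**The concern.** ORR is the primary endpoint, there is no control arm, and the test compares the observed rate with a fixed 25%. An ambiguity in who counts as a responder is therefore not offset by the same ambiguity in a comparison group.

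A patient with fewer than 5% marrow blasts, recovered counts and no flow result is a responder under 3.2.2. Under 8.4.1 the answer depends on whether an item that was not tested counts as met. Diagnosis is made locally (6.3.3), and reference review covers selected cases only (9.2.1), so two centres could score identical patients differently. A strict reading lowers the ORR; the 3.2.2 reading does not. Response also decides the switch to observation in 5.4.1, so the two sections must be reconciled for conduct as well as for analysis.

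**Working it through.** **1. The definitions side by side**

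| Item | 3.2.2 footnote | 8.4.1 |
|---|---|---|
| Marrow blasts < 5% | CR, CRp, CRi | CR, CRp, CRi |
| Neutrophil and platelet limits | yes | yes |
| Flow item | none | CR, CRp, CRi |
| Molecular negativity | none | CRi only |
| No blood blasts | none | CRp, CRi, but not CR |

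Section 8.4.1 also names Auer rods, extramedullary disease and, for CR, transfusion-independent haemoglobin. The footnote has none of these.

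**2. Where an untested patient goes under a strict reading of 8.4.1**

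Take < 5% blasts, recovered counts and no flow. The patient is then not CR, CRp or CRi. Partial remission needs 5–25% blasts, and stable disease needs persistent AML. The indeterminate group covers early death, death without an evaluable marrow, and an incomplete first course. No category fits.

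**3. The molecular item**

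Section 6.3.2 makes central molecular diagnosis optional and, in follow-up, limits it to patients with a marker at diagnosis. The CRi item therefore raises the same question of an absent result.

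**4. Exact values**

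Neutrophils of exactly 1,000/µl are neither > 1,000 (CR, CRp) nor < 1,000 (CRi). Platelets of exactly 100,000/µl with neutrophils above 1,000/µl are neither CR nor CRp.

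**5. The plan's own sample size**

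Inputs from 8.1 and 8.2: null 25%, one-sided alpha 0.025, power 80%, exact binomial test, intention to treat. Expected ORR = 0.50 × 0.13 + 0.35 × 0.87 = 0.3695, rounded to 37%.

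Normal approximation: n = [(1.96·√(0.25·0.75) + 0.8416·√(0.3695·0.6305)) / (0.3695 − 0.25)]² = 110.3, so 111. This reproduces the plan's 111 evaluable patients, and 111 + 11 = 122. The definition conflict does not alter this figure.

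**6. Illustration of what strict scoring could cost**

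Section 8.2 evaluates every included patient, so n = 122. The exact test then needs at least 41 responses (alpha 0.0206). Expected responders at 37% are 0.37 × 122 = 45.1, a margin of about 4. Let f be the share of true responders scored as non-responders for want of flow. The protocol gives no value for f, so a range is assumed. Measured ORR = 0.37 × (1 − f); power = P(X ≥ 41) for a binomial with n = 122.

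| f (assumed) | Measured ORR | Power |
|---|---|---|
| 0 | 37.0% | 80.7% |
| 5% | 35.2% | 67.2% |
| 10% | 33.3% | 50.5% |
| 20% | 29.6% | 19.1% |

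The measured ORR reaches the null at f = 1 − 0.25/0.37 = 32.4%. If the 3.2.2 definition is used, or if absent flow counts as no evidence, f = 0 and nothing is lost.

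**The case against.** **Flow is available.** A reader might infer from Table 2 that flow is never collected on treatment. The protocol does not support that. Section 6.1.2 allows baseline evaluations to be repeated, and 6.3.2 provides for follow-up material with immunophenotyping on request. Table 2 has no immunophenotyping row at baseline either, although 6.1.1 requires it then, so the table's silence proves little. What stands is that flow is not mandated at response.

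**The wording is permissive.** A reader might also infer that 8.4.1 demands a negative result, so that responders are necessarily lost. The item asks for no evidence of leukemia by flow, and an untested marrow can meet those words. Section 8.4, which does not name flow as an efficacy source, fits that view. Loss of responders is therefore one reading. That both readings are open is the defect.

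**Later marrows can rescue a response.** ORR counts response at any time, and 6.1.4 schedules a confirmatory marrow at 4 weeks and aspirates every three months. A responder is lost only if flow is missing at every qualifying marrow. This stands: if f is read as the share without flow at the first response marrow, the power losses are upper bounds.

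**The smaller points are minor.** It is tempting to say that a patient could be in CR and in relapse at once. Section 8.4.1 defines relapse as reappearance of blasts, which implies earlier clearance, so this goes too far. Exact count values should be rare and counts are repeated, so no effect on ORR is shown. The gaps remain in the text.

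**The analysis plan could supply a missing-data rule.** It could, but the conflict between 3.2.2 and 8.4.1 lies within the protocol.

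**Conclusion.** The point holds as a conflict of definitions. Sections 3.2.2 and 8.4.1 give different criteria for the same primary endpoint. The extra flow and molecular items in 8.4.1 have no stated rule for an absent result, so the ORR numerator is not determined and can vary with local practice.

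The protocol does not show that responders will be lost or how many. The fall in power from 80.7% to 67.2%, 50.5% or 19.1% is hypothetical. It rests on assumed losses of 5%, 10% or 20% of true responders, on missing flow being scored as non-response, and on a true ORR of 37% across all 122 patients. Under either of the other readings there is no loss.

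The missing blood-blast item in CR and the unclassified exact values are drafting faults with no demonstrated effect on ORR. The point should be settled before phase II data are assessed, because the correction is cheap and the endpoint is primary.

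**What to change.** - Use one definition of CR, CRp and CRi for the primary analysis, written identically in 3.2.2 and 8.4.1 (or have the footnote refer to 8.4.1).
- State there that an absent flow or molecular result does not remove a response.
- State in the same place whether a positive flow or molecular result does. If it does, a centre that tests can lose a responder and one that does not test cannot, so some dependence on local practice remains. If it does not, these results become supportive and the dependence disappears.
- Settle the CRi molecular item explicitly; at present it applies only in 8.4.1.
- Add absence of blood blasts to CR, as already required for CRp and CRi.
- Make the cut-offs contiguous, for example ≥ 1,000 versus < 1,000 neutrophils/µl and ≥ 100,000 versus < 100,000 platelets/µl.

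The cost is a wording amendment, with no extra test and no change to the sample size. The definition becomes slightly less stringent than mandatory flow. The loss should be small, since the stated flow sensitivity is the same 5% as the blast limit. Scheduling flow at every response marrow would also remove the ambiguity, at a higher cost.
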